### Outcomes

#### The primary outcomes

The primary outcome is the event-free survival, which is determined as the time from randomization to the time of a first recurrence in ipsilateral chest wall or in breast or in regional nodal or distant sites, a contralateral BC, or breast cancer specific death.

The secondary endpoints include the following outcomes: (1) local regional recurrence free survival, which is defined as the time from randomization to a first recurrence in ipsilateral chest wall or in breast or in regional nodal areas. (2) overall survival which is defined as the time from randomization to death from any cause.

#### Power and sample size calculation

The power and sample size are calculated according to the hypothesis that the 5-year event-free survival of omitting IMNI group is non-inferior to those patients treated with comprehensive RNI with IMNI. According to survival outcome of pN1 breast cancer in our institute, the 5-year event free survival (EFS) is estimated to be 91% for the control and 81% for experimental groups, respectively. The permissible limit for HR is 2.30, with statistical power of 80%, an alpha level of 0.025 (one-sided). With an anticipated enrolment period of 24 months, a total sample size of 208 patients is estimated to be needed. To compensate for eligible patients, the targeted number of patients is set at 214.

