Since IMNI would inevitably increase the lung and heart radiation dose, which might be related with an increased risk of developing cardiac or pulmonary toxicities [8]. Thus, in clinical practice, histological classification of breast tumors has been instrumental in determining a more personalized approach for pN1 breast cancer. Indeed, multiply studies have been performed to stratify clinical “high risk” early-stage BC patients who might be obtained from adjuvant post-mastectomy radiotherapy (PMRT) [9–14]. In consistent with those previous reports, our institution establishes and validates a prognostic nomogram including five risk factors (age, number of positive LN, tumor size, grade and Ki-67) accurately predict 5-year BC specific survival after mastectomy without adjuvant radiotherapy, which provides a practical stratification system to identify “high-risk” BC patients who might be indicated for adjuvant RT [15]. Subsequently, we validate this risk stratification model to individualize the adjuvant RT strategy among pT1-2N1 BC treated with modern systemic therapy, our result indicates that PMRT is an independent prognostic factor for DFS (HR 0.50, *p* = 0.05) among the clinical “high-risk” patients. However, those clinical “high-risk” patients could not benefit from comprehensive RNI with IMNI compared to those without IMNI (*p* > 0.05) [16]. In comparison with clinical risk model based on histopathologic factors, multi-genomic expression would provide individualized prognostic information for BC patients. Currently, multi-genomic expression profiling, such as 21-gene recurrence score and PAM-50-based 46-gene assay, has been recommended by international guidelines to tailor systemic therapy for patients with early-stage BC, but the clinical implications of multi-genomic expression for guiding radiotherapy is less well established. In a secondary analysis of a prospective trial of NSABP (National Surgical Adjuvant Breast and Bowel Project) B-14 and B-20,the authors find that the 21-gene Recurrence Score is an independent risk factor for locoregional recurrence in the cohort of 895 hormonal receptor (HR) positive patients treated with tamoxifen (HR2.16, 95%CI: 1.26–3.68, *p* = 0.005) [17]. In another retrospective analysis based on the Austrian Breast and Colorectal Cancer Study Group (ABCSG) 8 trial, the authors demonstrate that PAM-50 could be used to identify high local recurrence risk among postmenopausal HR-positive BC received with hormonal therapy, but it is not a predictive factor for obtaining from adjuvant RT [18]. RecurIndex, combined with 18 cancer genes and 10 reference genes, is a multigene profiling assay based on Chinese 28 genes, which could be used to predict the risk of local recurrence and distant metastasis for BC patients [19–22]. Our research team have demonstrated that the 5-year local–regional recurrence (LRR) free survival rates are 95–100% for N0 and N1 mastectomy BC patients with the 18-gene scores of < 44, while the LRR-free survival rate decreases to only 27–51% among BC patients with the 18-gene scores of more than 44 [23]. Thus, the 18-gene recurrence score might be used to identify biologically “high risk” breast cancer patients who would benefit from IMNI. Currently, to our best knowledge, there is no prospective studies to specifically investigate the role of IMNI in pN1 BC according to clinical-genomic model. As a result, we design this prospective trial by using an established clinical risk model combined with 28-gene score (RecurIndex) to individually stratify the risk of pN1 BC, and then to investigate whether those clinical “high-risk”, but genomic “low risk” pN1 BC patients would be safely omitting IMNI. Based on the Standard Protocol Items: Recommendations for Interventional Trials (SPIRIT) guidelines, our research team write the prospective trial protocol.

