### Objectives

The primary objective of this prospective non-inferior, RCT aims to investigate whether clinically “high risk”, but genomic score “low risk” early-stage BC would be safely omitted from IMNI.

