The current trial has several potential limitations. First of all, this is a single institute randomized controlled trial, and enrolling patients are performed at our institution, which might limit generalization of the result to other medical centers. Secondly, this is an open-label trial, both the participants and radiation oncologists are aware of the study group assignment, which might increase the selection bias. Thirdly, the primary outcome is 2-year event-free survival, and the follow-up is too short for observing events. After completing the trial, long-term follow-up of enrolled participants would be continued. Fourthly, the randomization of the present trial does not stratify according to risk factors, which might another source of heterogeneity. Finally, the 10% non-inferiority margin between the two groups might be larger in clinical practice, although this margin is discussed and decided by our clinical team.

In conclusion, the IMNI PRECISION trial is a non-inferior, randomized controlled trial to compare the survival and toxicity differences of omitting IMNI vs delivering IMNI in pN1 BC patients by using our established clinical risk model and multi-genomic model. We anticipate that our results would provide high-level evidence to tailor IMNI according to individualized recurrence risk of BC.

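### The sample-size section gives 81% as the estimated EFS without IMNI, although it is the rate implied by the non-inferiority limit, and the stated 80% power holds under neither reading

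*Protocol article*

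**What the plan says.** All references are to the protocol article.

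- Power and sample size calculation, hypothesis: "the 5-year event-free survival of omitting IMNI group is non-inferior to those patients treated with comprehensive RNI with IMNI".
- Same section, planning rates: "According to survival outcome of pN1 breast cancer in our institute, the 5-year event free survival (EFS) is estimated to be 91% for the control". The sentence continues so that 5-year EFS "is estimated to be 91% for the control and 81% for experimental groups, respectively". Both figures are worded as estimates.
- Same section, margin: "The permissible limit for HR is 2.30". Power is 80% at one-sided alpha 0.025, with 24 months of enrolment, 208 patients needed and a target of 214.
- Discussion, limitations: "the 10% non-inferiority margin between the two groups might be larger in clinical practice".
- Objectives: the question is "whether clinically “high risk”, but genomic score “low risk” early-stage BC would be safely omitted from IMNI". Trial design confirms that only pN1 patients with at least two clinical risk factors and a score of 44 or less are randomised.
- Background, on the institute's own clinically high-risk series: "those clinical “high-risk” patients could not benefit from comprehensive RNI with IMNI compared to those without IMNI", reported as p > 0.05.

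**The concern.** The power of a non-inferiority trial depends on two separate things: the limit to be excluded and the true difference assumed when power is calculated. The article gives the limit (2.30) but words the second figure as if omission were expected to cost 10 percentage points of 5-year EFS. That conflicts with the hypothesis in the same section. It also sits badly with the Background's report of no detectable IMNI benefit in clinically high-risk patients. A single figure cannot be both the worst acceptable outcome and the expected one.

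A second, smaller gap is the source of the rates. It is described only as pN1 patients at the institute, while the trial randomises a subgroup defined by clinical risk and genomic score.

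At stake is whether the trial can answer its question. If the stated power is not attached to a stated true scenario, nobody can judge from the article how likely an inconclusive result is.

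**Working it through.** **Inputs from the article.** Control EFS 91% and experimental EFS 81% at 5 years; HR limit 2.30; one-sided alpha 0.025; power 80%; 1:1 allocation; 24-month enrolment; N = 208, target 214; at least 5 years' follow-up per patient (Follow up section).

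**Assumptions added here.** Exponential event times, uniform accrual (so follow-up is uniform on 5 to 7 years), no dropout, all 214 analysed.

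**Step 1: what 81% is.**
- EFS implied by the limit: 0.91^2.30 = 0.805.
- Absolute difference: 91% − 81% = 10 points, the margin named in the Discussion.
- HR implied by 91% and 81%: ln(0.81)/ln(0.91) = 0.2107/0.0943 = 2.234, just inside 2.30.

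So 81% behaves as the boundary on both scales, up to rounding.

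**Step 2: events needed.** With equal arms, d = 4 × (1.960 + 0.842)² / (ln 2.30)² = 31.4/0.694 = 45.3. Rounded up, this is 46 events (the Freedman formula gives 51).

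**Step 3: can 208 be reproduced?** The hazard is λ = −ln(S)/5. The mean event probability is 1 − (e^(−5λ) − e^(−7λ))/(2λ).
- At 91%: 0.107. At 81%: 0.223. Average of the two: 0.165.
- 46 events with 91% in both arms: 46/0.107, about 431 patients.
- 46 events with 91% and 81%: 46/0.165, about 279 patients.

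Neither is 208. Figures near 208 appear only with inputs the article does not state, for example 81% in both arms (207), or one-sided alpha 0.05 on proportions with a 10-point margin and 91% in both arms (204).

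**Step 4: power at N = 214.** Power = Φ[ln(2.30/true HR) × √d/2 − 1.96].

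| True 5-year EFS (control / omission) | True HR | Expected events | Power |
|---|---|---|---|
| 91% / 81%, as worded | 2.234 | 35 | 3% |
| 91% / 91% | 1 | 23 | 51% |
| 88% / 88% | 1 | 30 | 63% |
| 95% / 95% | 1 | 13 | 32% |

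- First row: ln(2.30/2.234) = 0.029; 0.029 × √35.3/2 = 0.086; 0.086 − 1.96 = −1.87; Φ = 0.03.
- Second row: 0.833 × √22.9/2 = 1.993; 1.993 − 1.96 = 0.033; Φ = 0.51.

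A simulation that declared non-inferiority when the upper 97.5% Cox limit fell below 2.30 (4,000 runs, N = 214) gave 3.1% for 91/81, 51.3% for 91/91 and 30.9% for 95/95.

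**Step 5: sensitivity to follow-up.** With exactly 5 years per patient, 91/91 gives 19 events and 45% power. If the study closes 5 years after first entry, it gives about 15.5 events and 37.5%. The 91/81 reading stays at 3% in both cases.

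The 88% and 95% rows are illustrative, because the article gives no EFS for the randomised subgroup.

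**The case against.** The best defence is that 81% is plainly the margin. The Discussion calls 10% the margin, and 2.30 applied to 91% returns almost exactly 81%, so this is loose wording in a condensed article. That stands. A reader might infer that the investigators expected omission to be 10 points worse, and that the planning scenario itself is wrong. The documents do not support that, and equal arms at 91% may well have been intended. The 3% figure therefore describes the text as written and is not a forecast for the trial. For the same reason, an event count for 80% power at 91% against 81% would mean nothing: the distance to the limit is 0.029 on the log scale, and it vanishes if 81% is a rounded 80.5%.

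The defence does not rescue the 80%, since equal arms at 91% give 51%.

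Two further inferences are tempting and also fail:

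- **That the rates come from unselected pN1 patients and so do not fit the trial.** The article does not say how the source was selected, and a condensed article need not. Clinical high risk would tend to lower EFS and a low genomic score to raise it, so even the direction of a mismatch is unknown.
- **That the Background contradicts 91%.** It says "the 5-year local–regional recurrence (LRR) free survival rates are 95–100% for N0 and N1 mastectomy BC patients with the 18-gene scores of < 44". This is locoregional recurrence-free survival in mastectomy patients. The trial's EFS also counts distant recurrence, contralateral cancer and breast cancer death, and breast-conserving surgery is allowed. The two figures are compatible.

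Finally, the Background's IMNI comparison is reported only as non-significant, without an effect size or interval. It sits badly with an expected 10-point loss but does not disprove one.

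**Conclusion.** The point holds as a labelling and specification error with a numerical consequence. The sample-size section presents the boundary rate as the expected rate, never states the true EFS assumed without IMNI, and attaches 80% power to a scenario that does not deliver it. Power is about 3% if 81% is taken literally and about 51% (23 of about 46 events) if both arms are at 91%.

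These figures rest on exponential event times, 5 to 7 years' follow-up and no dropout. Dropout or shorter follow-up would lower the 51%. The limitations paragraph refers to a 2-year primary outcome. The check uses 5 years, as the Participants and sample-size sections do, and analysis at 2 years would yield fewer events still.

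On the source of the rates, only this can be said: the article does not show that 91% applies to the randomised subgroup, and it gives no EFS from which to judge. The shortfall under equal arms is the same one that any check of the sample size would find. It should be reported together with that point and counted once.

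**What to change.** In Power and sample size calculation:

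1. Describe 81% as the 5-year EFS implied by the HR limit of 2.30 at a control rate of 91%, not as the estimate for the experimental group, and align this with the 10% margin in the Discussion.
2. State the true 5-year EFS assumed in each arm for the randomised subgroup. For power under the non-inferiority hypothesis, this means equal arms.
3. Restate the power of 214 patients at that rate with a range, for example about 63% at 88%, 51% at 91% and 32% at 95%, and state the accrual, follow-up and dropout assumptions.
4. Say which patients the control rate comes from. If the institute holds EFS data on clinically high-risk patients with a score of 44 or less, preferably treated with IMNI, use them. The article does not show that such a cohort exists. If it does not, say so and rely on the range.

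The cost is protocol wording, possibly a re-analysis of institutional data, and a less favourable stated power. These corrections need no extra patients, but they only disclose the shortfall and do not remove it. With 75 patients enrolled by 30 July 2022, the article describes a trial still recruiting, so the text can be corrected before analysis.

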### Current trial status

The trial has been approved by the Ethics Committee of Ruijin hospital, Shanghai Jiao Tong University School of Medicine (RJ 2020–250) on 14 August 2020 and registered on ClinicalTrials.gov (NCT04517266) before recruitment. The currently used trial protocol version is Version 2.0 (December 2020). The recruitment of the trial is initiated on 10 December 2020. At present, the IMNI PRECISION trial remains at the recruiting stage and a total of 75 patients have been enrolled until 30 July 2022. We would publish the survival outcome of patients enrolled in the present trial after completing the trial and long-term follow-up.

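### The stated sample-size inputs give about 50% power on the hazard-ratio scale, not 80%: 208–214 patients yield 22–23 expected events where about 45 are needed

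*Protocol article*

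**What the plan says.** Everything needed to check the figure is in the protocol article. Under Power and sample size calculation, the margin and error rates are given as "The permissible limit for HR is 2.30, with statistical power of 80%, an alpha level of 0.025 (one-sided". The survival assumption is that "the 5-year event free survival (EFS) is estimated to be 91% for the control and 81% for experimental groups, respectively". The result follows: "With an anticipated enrolment period of 24 months, a total sample size of 208 patients is estimated to be needed". The target is then raised to 214. Allocation is 1:1 (Trial design; Allocation), and the Follow up section promises at least 5 years for each patient after radiotherapy. No required number of events is stated.

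Two other places bear on the scale of the comparison. The Participants section states the aim as a non-inferiority comparison of the difference in 5-year EFS. The limitations paragraph of the Discussion says that "the 10% non-inferiority margin between the two groups might be larger in clinical practice".

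**The concern.** In a time-to-event non-inferiority test, power depends on the number of events. A control arm with 91% EFS at 5 years produces few of them: roughly one patient in ten over the planned follow-up. Some 20 events from just over 200 patients looks too few to exclude a hazard ratio of 2.30 with 80% power. The wording adds to the doubt, because 81% is called the estimate for the experimental arm although it sits almost exactly at the non-inferiority limit.

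At stake is the chance that the trial answers its primary question. If omission is truly equivalent, the text implies a 20% risk of failing to show non-inferiority. At 50% power that risk is one in two.

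**Working it through.** **Inputs.** HR limit 2.30, one-sided alpha 0.025 (z = 1.960), power 80% (z = 0.842), control 5-year EFS 91%, 24-month enrolment, N = 208 and 214 (all from Power and sample size calculation); minimum follow-up 5 years (Follow up); 1:1 allocation. Assumptions added here: true HR of 1, so 91% in both arms; exponential event times; uniform accrual; no dropout.

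**Attempt to reproduce 208**

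1. Events needed (Schoenfeld): 4 × (1.960 + 0.842)² / (ln 2.30)² = 4 × 7.85 / 0.694 = 45.3.
2. Hazard: −ln(0.91)/5 = 0.01886 per year.
3. Event probability with uniform 2-year accrual plus 5 years: 1 − [exp(−5λ) − exp(−7λ)]/(2λ) = 1 − (0.9100 − 0.8763)/0.03772 = 0.107.
4. Patients needed: 45.3/0.107 ≈ 423. The stated 208 is not reproduced.

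**Power at the stated sample size**, from Φ(√(D/4) × ln 2.30 − 1.960), where D is the number of events:

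- N = 208: D = 22.2; Φ(0.00) = 50%.
- N = 214: D = 22.9; Φ(0.03) = 51%.
- Simulation of the same design for N = 208 gave 50–52%.
- Largest observed HR that still excludes 2.30: exp(0.833 − 1.960 × 2/√D), about 1.00 for 22.2 events and 1.01 for 22.9.

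**Other readings that keep 91% for control, one-sided 0.025 and the 5-year horizon**

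| Reading | N = 208 | N = 214 |
|---|---|---|
| HR scale, each patient counted to exactly 5 years (18.7; 19.3 events) | 44% | 45% |
| HR scale, 91%/81% used only to count events (34.3; 35.3 events) | 68% | 70% |
| 10-point difference in 5-year EFS, 91% in both arms | 71% | 72% |

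For the last row, the number needed is 2 × 2 × 0.91 × 0.09 × (2.802)²/0.10² = 257. At 104 per arm the standard error is √(2 × 0.91 × 0.09/104) = 0.0397, and Φ(0.10/0.0397 − 1.960) = Φ(0.56) = 71%.

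**Where a figure near 208 does appear.** With 81% EFS in both arms, HR limit 2.30, one-sided 0.025 and 24 months plus 5 years, the requirement is 203 patients; 208 give 46.4 events and 81% power. This replaces the stated control rate of 91%.

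**What 81% is.** 0.91^2.30 = 80.5%, and 91% minus 10 points is 81%. The value is the limit on either scale.

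**Sensitivity to accrual.** Current trial status reports that "a total of 75 patients have been enrolled until 30 July 2022", counted from 10 December 2020. That is 75 in 19.6 months, or 3.8 per month. At a constant rate 214 patients would take about 56 months. With that accrual plus 5 years, 208 patients give 26.8 events and 58% power.

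**The case against.** The strongest reply is that the shortfall depends on choices the article leaves open. Trial design has participants followed until death or drop-out, and no analysis date is fixed. At 91% in both arms, 208 patients reach 80% power with about 12 years of minimum follow-up (45.2 events). The article also condenses a fuller protocol. And since the aim is worded as a difference in 5-year EFS with a 10-point margin, 71–72% may be the fairer figure than 50%.

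The last part stands: the size of the shortfall depends on the scale, and both figures should be given. The rest does not rescue the 80%. The hypothesis is set at 5 years, no 12-year analysis is stated, and a fuller document cannot make these published inputs yield 208.

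Four stronger conclusions that a reader might infer are not supported:

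- **That no reading reaches 80% at one-sided 0.025.** Using 81% in both arms does, as does very long follow-up. The first contradicts the stated control rate and the second is not planned, but an absolute claim would be false.
- **That power is about 3%.** This follows from taking 81% as the true experimental EFS (HR ln 0.81/ln 0.91 = 2.23 against 2.30). The 10-point margin in the Discussion and 0.91^2.30 = 80.5% show that 81% is the limit, loosely labelled an estimate.
- **That slow recruitment contradicts the calculation.** The 24 months was a planning assumption, and the 75 patients are later status. Slower accrual with the same minimum follow-up raises power somewhat.
- **That 208 was a particular slip.** Using 81% in both arms is one possible source; the document does not settle it.

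**Conclusion.** The concern holds. On the stated hazard-ratio scale, 208–214 patients give 22–23 expected events against about 45 required, and power of 50–51% where 80% is claimed. Read as a 10-point difference in 5-year EFS, the shortfall is smaller: 71–72%, with about 257 patients needed. These figures rest on a true HR of 1, exponential event times, uniform 24-month accrual, 5 years of minimum follow-up and no dropout; dropout would lower power further. The direction of the error is the same on every reading examined that keeps the stated control rate, alpha and 5-year horizon. Its size is not, and it depends on a choice of scale that the article does not make clear.

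**What to change.** Restate the sample-size paragraph:

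1. Call 81% the non-inferiority limit (0.91^2.30 = 80.5%), not the estimated experimental EFS, and state that 91% is assumed in both arms under the alternative.
2. Give about 45 events as the requirement for 80% power, 22–23 as the number expected from 208–214 patients, and the resulting power of about 50% on the HR scale. If the 10-point difference in 5-year EFS is the intended measure, give about 71%.
3. Say which scale decides non-inferiority.
4. Optionally report power at the observed accrual rate (about 58%) as a sensitivity figure, leaving the original 24-month assumption visible.

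This costs a rewording and no extra patients; the price is a less favourable stated power. It makes the claim accurate but does not restore 80%. That would take about 423 patients on the HR scale, about 257 on the difference scale, or much longer follow-up, which is for the sponsor to weigh. Moving to the 5-year difference merely to gain power is a trade-off and not a correction: patients are already randomised in an open-label trial, and power would still be only about 71%.
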